#### 3.3.3. Contexts and Measurement Frequencies

Four sessions will be held, each divided into two parts:

Selection of dependent variables: The objective of the initial two sessions is to establish a baseline for physiological variables during activities that elicit both positive and negative emotions, to use this baseline as a reference in Part 2. The goal is to minimize the reliance on the EVEA tests, as participants may not always be able to articulate their emotions. The EVEA test serves as a supporting tool for a potential automatic classifier.

Session 1: Measurement of parameters when the subject is conducting a pleasurable daily-life activity in the center.Session 2: Measurement of parameters when the subject is conducting an uncomfortable daily-life activity in the center.These sessions will be determined by conversation with the caregivers since they are specific to each subject.

Half of the participants will start with session 2 and then do session 1, while the rest will follow the reverse order.

Music’s influence on the dependent variables: The aim of the next two sessions is to determine the music’s influence on the dependent variables while conducting rehabilitation exercises.

Session 3: Measurement of subject parameters during the performance of rehabilitation activities in the center.Session 4: Measurement of subject parameters during rehabilitation activities in the center. This session will be accompanied by music according to the preferences of the subject.

Each participant will select the music to be played in each session according to their musical preference or, failing that, the music will be selected by their caregiver. The rehabilitation activity should be a gentle exercise for the participant, such as pedaling, extending the limbs or any other activity that can be quantified using inertial units. Furthermore, these activities should be determined by the medical/physiotherapist staff according to the capabilities of each volunteer.

Even though every session has a unique theme, the format of the sessions will remain consistent. The sensors will initially be placed on the participant and a data acquisition test will be performed to ensure that all data are being captured correctly. Data recording will initiate while the user is responding to the EVEA test; this phase will be used as a baseline for the session—note that a minimum of two minutes is required. The following phase will be the main activity, with a 15 min time limit, ending with a final EVEA test with identical specifications to the initial one, which will be used as the final baseline. Both baselines allow for the detection of the measurement differentials in each session, alongside the analysis of the participant’s progression during the activity. Each participant is expected to finish the protocol within two weeks, where the first and second sessions will be scheduled for the first week, and the third and fourth sessions will be set for the second one. Figure 4 shows a diagram of the described protocol.

## 4. Statistical Methodology

### 4.1. Sample Size

The population of the centers is approximately 200 individuals (100 from each center, adults and children). According to Cochran’s formula for estimating the sample, assuming, in the worst-case scenario, a value of *p* = *q* = 0.5 (maximum variance), a confidence interval of 95% and a margin of error of 15%, the sample size would be 36 individuals. Therefore, a sample size with 18 adults and 18 children seems adequate.

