The challenge we propose to address is that people with severe disabilities struggle to disclose and identify emotional states, which eliminates the possibility of utilizing self-assessment tests for comparison with the collected measures. This requires us to rely on their caregivers, or, alternatively/additionally, to implement measures in everyday scenarios or contexts where the emotional state elicited in the individual is understood.

This experimentation is part of a subproject called AAI (Augmentative Affective Interface), which in turn is part of the AIR4DP (Artificial Intelligence and Robotic Assistive Technology devices for Disabled People) coordinated project that is funded by the Ministry of Science, Innovation and Universities (I+D+i Projects 2019— Society Challenges). The main expected result of the AIR4DP project is the implementation of assistive technology that allows incorporating the latest advances in artificial intelligence (AI) to improve the quality of life of people with disabilities. The AAI subproject seeks an improvement in users’ interaction with systems achieved through knowledge of their emotional state based on physiological measurements and imagery. If this knowledge were injected into a robotic platform or a software platform used in rehabilitation therapies, a greater immersion and motivation of the subject in the proposed activities could be achieved.

The structure of the current paper is as follows. First, a review of the state of the art is presented, taking into account current knowledge on the factors involved in the study of emotional state, the target population (people with CP) and the influence of music on the state of mind. Subsequently, in Section 3, the methodology of the proposed experimentation is described. The type of study and the criteria for the inclusion and exclusion of participants are indicated. The instruments used to carry out the measurements to determine the state of the subjects are listed and explained; these instruments include measurement scales and physiological measurements. Section 4 shows that the chosen sample size is adequate and explains the statistical analysis that will be carried out with the collected data. Finally, in Section 5, we conclude by establishing the importance of designing an experimental protocol in accordance with the characteristics of the subjects that allows for the objectives set out in the protocol to be met.

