### 3.2. Participants

The participants, as already indicated, belong to the ASPACE association (adults) and the Director Mercedes Sanromá Special Education School (children). The study will involve 40 subjects: 20 adults and 20 children. The following criteria are proposed for this group of participants.

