### 4.2. Data Analysis

In general, numerical variables will be expressed as mean (M) and standard deviation (SD), including range, minimum and maximum.

For the first part of the study, we will compare the dependent variables obtained between sessions 1 and 2 for each subject using the permutation test of the difference in means between different data windows. Those dependent physiological variables that mark significant differences for most of the subjects will be chosen. Changes in EVEA test responses between sessions 1 and 2 will serve as reinforcement for detecting the level of emotional change.

We will also correlate the results of the EVEA test with the base state questionnaires to determine the existence of some type of dependency between the base level of EVEA and its variation with respect to the base state. This dependence will be explored with the Spearman or Pearson correlation test.

For the second part, first, we will analyze the variation in EVEA for sessions 3 and 4 to determine if there is a significant dependence on the independent variable (music) between stages A and B for all the participants. We will use the Kruskal–Wallis test, which does not require any type of assumption regarding the normality and homoscedasticity of the samples. These variations will also be correlated with the quality of life scale (ICF, GMFCS, MACS, CFCS, or KIDSCREEN), as was carried out with the data from the first part.

For the physiological variables and the average kinetic energy, we will determine if their variations are significant between A and B by means of a Kruskal–Wallis test applied to the group of subjects, but also at the individual level by means of a permutation test.

The significance of the tests will be set at three levels, indicated with * (*p* < 0.05), ** (*p* < 0.01) and *** (*p* < 0.001).

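### The sample size is called adequate from a survey formula for one proportion, but no planned analysis estimates a proportion, so adequacy is not shown for any planned test

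*Protocol article*

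**What the plan says.** Section 4.1 (Sample Size) takes the two centres as one population: "The population of the centers is approximately 200 individuals (100 from each center, adults and children"). It names its method, "According to Cochran’s formula for estimating the sample", takes p = q = 0.5 as the "maximum variance" case, and states: "a confidence interval of 95% and a margin of error of 15%, the sample size would be 36 individuals". It concludes: "Therefore, a sample size with 18 adults and 18 children seems adequate". The Introduction presents this as something demonstrated: "Section 4 shows that the chosen sample size is adequate".

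Section 3.2 (Participants) gives another number: "The study will involve 40 subjects: 20 adults and 20 children".

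Section 4.2 (Data Analysis) sets out what will be done with the data:
- Sessions 1 and 2 are compared within each subject "using the permutation test of the difference in means between different data windows".
- EVEA results are correlated with the base-state questionnaires (Spearman or Pearson).
- Session 3 (condition A, silence) is compared with session 4 (condition B, music) at group level by Kruskal–Wallis. For the physiological variables and kinetic energy it is also compared within each subject by a permutation test.

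Section 4.1 gives no effect size, standard deviation or power for any of these.

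**The concern.** Cochran's formula answers one question: how many people must be drawn at random from a population so that an estimated percentage lies within a chosen margin of the true one. This study asks other questions: whether a signal differs between a pleasant and an uncomfortable activity, whether music changes mood, physiology or movement, and whether mood change relates to baseline scales. A 15-point margin on a percentage carries no information about any of these.

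The formula's sampling assumption also fails. It presumes a random sample of the 200 attendees, whereas Section 3.2.3 invites everyone who meets the inclusion criteria.

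The stake is interpretation. A reader told that adequacy has been shown may take a non-significant music comparison as evidence that music does nothing, although no detectable effect was ever stated.

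**Working it through.** **1. The plan's own figure.** Inputs from Section 4.1: p = q = 0.5, z = 1.96, margin e = 0.15, N = 200.
- n0 = z²pq/e² = 1.96² × 0.25 / 0.15² = 42.68
- With finite-population correction: n = n0 / (1 + (n0 − 1)/N) = 42.68 / (1 + 41.68/200) = 35.3, so 36. The figure reproduces.
- Margin reached with 36 of 200: 1.96 × 0.5 × √(164 / (199 × 36)) = 0.148, i.e. 14.8%.

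**2. Match to the analyses.** Each analysis in Section 4.2 set against the formula:
- Per-subject permutation tests: a difference in means over data windows. Not a proportion.
- Spearman or Pearson correlations: not a proportion.
- Kruskal–Wallis, A against B: a comparison of distributions. Not a proportion.
- Choice of variables that are significant in most subjects: a majority count, the nearest thing to a proportion. It has no interval or margin, and Section 4.1 does not refer to it.

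**3. What the numbers can detect.** The article gives no power, so 80% power and a two-sided 5% level are assumed here.

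*Paired group test (paired t, noncentral t distribution).* The normal approximation is (1.96 + 0.84)/√n, i.e. 0.44 for n = 40 and 0.47 for n = 36. The exact t solution is **0.45** and **0.48** SD of the paired difference. The signed-rank test is close to this.

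*Kruskal–Wallis as written.* It takes A and B as independent samples, so its critical value rests on a standard error of √(2/n) raw SDs. The true standard error of the mean difference is √(2(1 − ρ)/n), where ρ is the A–B correlation within subjects. The article gives no ρ. With ρ = 0.5 the paired-difference SD equals the raw SD, since √(2 × 0.5) = 1. For n = 40 the effect needed is roughly 1.96 × √(2/40) + 0.84 × √(1/40) = 0.438 + 0.133 = 0.57 SD, before the small losses from the rank method. Simulation with normal data puts it at about **0.6** SD. Simulated power of Kruskal–Wallis with 40 subjects when the true paired effect is 0.454 SD:

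| A–B correlation (assumed) | Power, about |
|---|---|
| 0 | 80% |
| 0.3 | 66% |
| 0.5 | 50% |
| 0.7 | 23% |

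*Correlations (Fisher z):* |r| = tanh((1.96 + 0.84)/√(n − 3)).

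| n | Detectable \|r\| |
|---|---|
| 40 | 0.43 |
| 36 | 0.45 |
| 20 | 0.59 |
| 18 | 0.62 |

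The last two rows matter because Section 3.3.1 assigns the ICF to adults and MACS, GMFCS, CFCS and KIDSCREEN to children. A correlation with any one of them rests on 18 to 20 people, unless scales are harmonised across ages. Section 3.2.1 mentions harmonisation only in connection with motor function.

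*Per-subject permutation tests.* Their sensitivity depends on the number and dependence of data windows within a subject. Neither 36 nor 40 enters.

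**The case against.** Several points in the plan's defence are sound.

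- **The arithmetic is right.** A reader might infer that 36 is miscalculated. It is not.
- **No margin is promised per age group.** A reader might infer that the plan breaks its own 15% criterion, because 18 of 100 gives 1.96 × 0.5 × √(82/(99 × 18)) = 21.0% and 20 of 100 gives 19.7%. But Section 4.1 states the margin for the pooled 36, where it is met, and Section 4.2 plans no adult-only or child-only music test. The smaller groups matter only for the age-specific correlations, which a margin on a proportion would not govern anyway.
- **Using all 200 attendees does not flatter the result.** A smaller eligible population lowers the requirement: with an assumed 120 eligible, 42.68/(1 + 41.68/120) = 31.7, so 32. The objection is that the sample is not random and the target is the wrong quantity, not that N = 200 makes 36 too small.
- **36 and 40 need not conflict.** One is a size judged sufficient and the other a larger planned number. A reader might infer that the extra four allow for dropout, but the article nowhere mentions dropout. The gap is unexplained, and only the sponsor can explain it.
- **Part 2 is described as a single-case AB study for each subject** (Section 3.1). For that layer the number of subjects is not the main driver of sensitivity. This is correct, and it is a further reason why Cochran's formula cannot establish adequacy.

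None of this links the formula to a planned test.

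**Conclusion.** The point holds as a mismatch between rationale and analysis. The number 36 is computed correctly, but for a quantity the study does not estimate, so the adequacy claimed in Section 4.1 and repeated in the Introduction is not established for any planned test.

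It does not follow that the sample is too small. The article states no effect of interest, so neither adequacy nor inadequacy can be shown from it.

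The size depends on the group test. At an assumed 80% power and two-sided 5% level, a paired test detects 0.45 SD (40 subjects) or 0.48 SD (36 subjects) of the paired difference. Those figures do not carry over to Kruskal–Wallis, which at an assumed A–B correlation of 0.5 needs about 0.6 SD with 40. Correlations confined to one age group can detect only |r| of about 0.6.

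**What to change.** 1. Keep the planned enrolment. Remove the Cochran argument as proof of adequacy from Section 4.1, and amend the corresponding sentence in the Introduction.
2. In its place, state the detectable effect for the group-level A–B comparison under the test that will be used. If that test is made paired (for example signed-rank), quote about 0.45 SD of the paired difference with 40 subjects or 0.48 with 36, at 80% power and two-sided 5%. If Kruskal–Wallis stays, these figures must not be quoted. Give instead the effect for that test with the assumed A–B correlation (about 0.6 SD with 40 at a correlation of 0.5).
3. Add that correlations with scales used in one age group only (18 to 20 subjects) can detect only |r| of about 0.6.
4. Add that the per-subject permutation tests depend on the data windows per subject, not on 36 or 40.
5. Reconcile 36 in Section 4.1 with 40 in Section 3.2, with the sponsor giving the reason.

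The cost is one rewritten paragraph and one amended sentence, plus a change of group test if the paired option is taken. No extra participants or sessions are needed. The stated sensitivity will look less reassuring, most of all for the age-specific correlations.

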### 4.2. Data Analysis

In general, numerical variables will be expressed as mean (M) and standard deviation (SD), including range, minimum and maximum.

For the first part of the study, we will compare the dependent variables obtained between sessions 1 and 2 for each subject using the permutation test of the difference in means between different data windows. Those dependent physiological variables that mark significant differences for most of the subjects will be chosen. Changes in EVEA test responses between sessions 1 and 2 will serve as reinforcement for detecting the level of emotional change.

We will also correlate the results of the EVEA test with the base state questionnaires to determine the existence of some type of dependency between the base level of EVEA and its variation with respect to the base state. This dependence will be explored with the Spearman or Pearson correlation test.

For the second part, first, we will analyze the variation in EVEA for sessions 3 and 4 to determine if there is a significant dependence on the independent variable (music) between stages A and B for all the participants. We will use the Kruskal–Wallis test, which does not require any type of assumption regarding the normality and homoscedasticity of the samples. These variations will also be correlated with the quality of life scale (ICF, GMFCS, MACS, CFCS, or KIDSCREEN), as was carried out with the data from the first part.

For the physiological variables and the average kinetic energy, we will determine if their variations are significant between A and B by means of a Kruskal–Wallis test applied to the group of subjects, but also at the individual level by means of a permutation test.

The significance of the tests will be set at three levels, indicated with * (*p* < 0.05), ** (*p* < 0.01) and *** (*p* < 0.001).

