In addition, we want to evaluate how music can be a motivational factor that improves the quality and time dedicated to physical exercise. Therefore, in the proposed experimental protocol, we will introduce an analytical study of type AB in the second part. In Section 2, the review of the state of the art, we presented previous studies with the common finding that musical parameters can induce emotions and the measurement of the EEG signal can be a primary method for showing their change. The proposed protocol will take these factors into account when choosing music and will also introduce the measurement of other types of additional physiological signals.

To operationalize this, sessions 3 and 4 of the experimental protocol have been devised. Music is introduced as a motivational element, and its impact is assessed using the parameters established in sessions 1 and 2. The goal is to enable subjects to invest more time and effort in their rehabilitation sessions, as the achievement of an optimal emotional and physical state during these sessions can be reliably and objectively monitored.

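### The per-subject permutation test on the difference in means, with no studentisation stated, holds its level for equal means only if the two sessions match in number of windows or in spread, and the plan guarantees neither

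*Protocol article*

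**What the plan says.** Protocol article, 4.2: for Part 1, each subject's sessions 1 and 2 are compared "using the permutation test of the difference in means between different data windows". A physiological variable is kept if it is significant in a majority of subjects. For Part 2, the physiological variables and kinetic energy are compared between silence and music by a group Kruskal–Wallis test, "but also at the individual level by means of a permutation test"; no statistic is named there. "The significance of the tests will be set at three levels": 0.05, 0.01 and 0.001. The remark that homoscedasticity is not needed is made for the Kruskal–Wallis test only.

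Protocol article, 3.3.3: across sessions "the format of the sessions will remain consistent". On duration: "The following phase will be the main activity, with a 15 min time limit". No minimum is given for the activity; the two-minute minimum ("note that a minimum of two minutes is required") applies to the baseline phases. On sessions 1 and 2: "These sessions will be determined by conversation with the caregivers since they are specific to each subject". The article gives no window length, window count or within-session SD.

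**The concern.** The stated question is whether a variable's mean differs between two sessions. Shuffling windows between sessions and recomputing the plain difference in means generates the null that all windows come from one distribution, with the same variance as well as the same mean. For large samples the two nulls give the same test only if the window counts or the variances are equal.

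The plan secures neither. Activity time is bounded only from above. Sessions 1 and 2 are different activities, one chosen to be pleasant and one uncomfortable. Variables listed in 3.3.2, such as kinetic energy, SCR and pNN50, could plausibly change in spread as well as level.

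Section 3.1 describes Part 2 as a single-case AB study for each subject, so the individual tests matter. A significance star could reflect session length and variability rather than a shift in mean. In the opposite configuration a real shift could be missed and its Part 1 vote lost.

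**Working it through.** **The plan's own figures.** No error rate or power is stated for the permutation test. The only computed figure is the sample size in 4.1, and it reproduces: 1.96² × 0.25 / 0.15² = 42.68; 42.68 / (1 + 41.68/200) = 35.32, rounded up to 36.

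**Inputs.** From the article: the test and the 5% level (4.2), and the 15-minute cap (3.3.3). Assumed: two-sided testing, independent normal windows, equal true means, length ratios 1:1 to 1:5, SD ratios 1.5 to 3.

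**Formula.** With window counts n₁, n₂ and SDs s₁, s₂, the true variance of the mean difference is s₁²/n₁ + s₂²/n₂. The permutation variance tends to s₁²/n₂ + s₂²/n₁. Hence

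size = 2 × (1 − Φ(1.96 × √(Vperm/Vtrue))).

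**Shorter session more variable, lengths 1:3, SD ratio 2.** Vtrue = 4/1 + 1/3 = 4.33; Vperm = 4/3 + 1/1 = 2.33; 1.96 × √(2.33/4.33) = 1.44; size 15.0%. Other settings, same formula:

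| Length ratio | SD ratio 1.5 | SD ratio 2 | SD ratio 3 |
|---|---|---|---|
| 1:1 | 5.0% | 5.0% | 5.0% |
| 1:1.5 | 7.0% | 8.2% | 9.5% |
| 1:2 | 8.5% | 11.0% | 13.6% |
| 1:3 | 10.7% | 15.0% | 19.9% |
| 1:5 | 13.2% | 19.9% | 28.0% |

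**Longer session more variable, lengths 1:3, SD ratio 2.** Vtrue = 1 + 4/3 = 2.33; Vperm = 1/3 + 4 = 4.33; the effective cut-off is 1.96 × √(4.33/2.33) = 2.67, so size is 0.8%. At a shift that gives a correctly scaled test 80% power (2.80 standard errors), power is Φ(2.80 − 2.67) = 55%, a loss of about 25 points.

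**Simulation** (2000 data sets, 999 permutations), rejection at equal means, plain / studentised:

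| Windows, short vs long | SD ratio | Shorter more variable | Longer more variable |
|---|---|---|---|
| 30 vs 30 | 2 | 4.4% / 4.4% | 5.7% / 5.7% |
| 20 vs 30 | 2 | 8.2% / 5.4% | 2.8% / 5.0% |
| 20 vs 30 | 3 | 11.3% / 6.7% | 2.9% / 5.5% |
| 10 vs 30 | 2 | 15.5% / 5.9% | 0.9% / 5.1% |
| 10 vs 30 | 3 | 21.6% / 6.4% | 0.6% / 4.0% |
| 5 vs 15 | 3 | 24.2% / 8.2% | 0.6% / 3.5% |
| 30 vs 90 | 2 | 15.1% / 5.8% | 0.9% / 4.9% |

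At a fixed length ratio, more windows do not cure the problem.

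**Power, longer session more variable**, plain vs studentised. At 10 vs 30 windows: 51.7% vs 74.5% (SD ratio 2) and 38.7% vs 74.9% (SD ratio 3), losses of 23 and 36 points. At 5 vs 15 windows with a true difference of 3 standard errors: 55% vs 73% and 43% vs 73%, losses of 18 and 30 points. At 20 vs 30 windows the loss is 8 to 11 points; at equal counts it is zero.

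**Majority rule.** At 20% rejection per subject, and with independent subjects, a null variable reaches at least 19 of 36 subjects with probability 1.3 × 10⁻⁵, and at least 21 of 40 with probability 5 × 10⁻⁶.

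**Serial correlation.** With AR(1) windows at 0.5, the studentised test rejects at 27% with equal lengths and equal SD, and at 26% with 10 vs 30 windows and the shorter session at twice the SD.

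**The case against.** The strongest reply is that the trigger is assumed. Distortion needs unequal window counts and unequal spread together. The article gives one session format and one cap, and states no duration difference, SD or window count. If both activities run to the cap, the problem vanishes. This stands, and it is why the size must be given as a range starting at 5%. It does not remove the point: a common format and an upper limit do not fix equal durations.

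A reader might infer from the Conclusions ("The goal is to enable subjects to invest more time and effort in their rehabilitation sessions") that session 4 will outlast session 3. The article does not say so. That sentence is a general aim, both sessions share the cap, and 3.3.3 describes a gentle exercise set by clinical staff.

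It can also be said that a condensed article leaves scaling and window counts to a fuller document. For window counts that is fair. For Part 1, however, the article names the statistic as a difference in means. For Part 2 it names none, so extending the point there is an inference.

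Finally, if spread differs, the sessions do differ, so rejection is arguably not false. But 4.2 frames the comparison as one of means. The test would also serve poorly as a test of any difference: when the longer session is the more variable, it rejects less than 5% of the time.

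**Conclusion.** The point holds as a cheap improvement to the stated method, not as a demonstrated failure of the trial. Under independent normal windows, the level runs from 5% (equal lengths) through about 7–10% (1:1.5) to about 15–25% (1:3, shorter session at 2–3 times the SD). In the reverse configuration at 1:3, rejection falls to about 2% or less and power drops by about 18–36 points. All length and SD ratios are assumptions.

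Two stronger readings are not supported. Three to four times nominal is neither what the trial will show nor an upper bound: 1:5 with SD ratio 3 gives 28%, and equal lengths give 5%. Nor does this defect on its own carry null variables through Part 1 selection, given the majority rule. What is exposed is the individual-level significance in both parts and the votes lost in Part 1.

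**What to change.** In 4.2, name a Welch-studentised difference in means as the permutation statistic, for Part 1 and for the individual tests of Part 2. In addition or instead, compare the same number of windows from matched elapsed time in both sessions, truncating to the shorter activity.

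Cost: one sentence and about one line of code, with no new data. Truncation discards some windows of the longer session. Studentising discards none, but costs a little power when spreads are equal and windows few (68.0% vs 73.4% at 5 vs 15 windows; 75.8% vs 78.1% at 10 vs 30). With very few windows it is also imperfect: about 8–10% rejection at 5 vs 15 with SD ratio 3.

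Neither change handles serial correlation between adjacent windows. That needs its own provision, such as permuting blocks of windows, and this fix should not be presented as making the test valid without it.

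### The per-subject permutation test shuffles windows that are not exchangeable between two single sessions, so its individual p-values are not valid, in Part 1 or in Part 2

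*Protocol article*

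**What the plan says.** Section 4.2 (Data Analysis) sets the Part 1 comparison for each subject separately, "using the permutation test of the difference in means between different data windows". The selection rule follows: "Those dependent physiological variables that mark significant differences for most of the subjects will be chosen". It does not say whether the differences must go in the same direction. On the threshold, "The significance of the tests will be set at three levels", of which 0.05 is the loosest.

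Section 3.3.3 (Contexts and Measurement Frequencies) gives each subject one session per condition: "Session 1: Measurement of parameters when the subject is conducting a pleasurable daily-life activity in the center" and "Session 2: Measurement of parameters when the subject is conducting an uncomfortable daily-life activity in the center". The activities are chosen for each subject with the caregivers. Sensors are placed at the start of every session. The recording then covers a start phase of at least two minutes, of which the article says "this phase will be used as a baseline for the session", the "main activity, with a 15 min time limit", and a closing baseline. Of the two baselines it says: "Both baselines allow for the detection of the measurement differentials in each session". Session order is reversed for half of the participants.

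In Part 2, section 4.2 uses an individual-level permutation test again, for exercise without and with music, alongside a group-level test.

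**The concern.** A permutation test holds its nominal level only if the shuffled units are exchangeable under the null. Here the unit shuffled is the window, while the condition belongs to the session. Two features break exchangeability:

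- Windows cut from one continuous ECG, EDA or EEG recording cannot be presumed independent.
- All windows of a session share that session's sensor placement, day and activity. Any shift in level between two recordings looks like an effect of emotion. The article itself warns, in its Introduction and Conclusions, that effort and movement disturb the signals.

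Part 1 counts individually significant subjects to choose the emotion markers, and the Conclusions say that the effect of music is then assessed with those markers. If ordinary session-to-session variation produces significant results in many subjects, a variable unrelated to emotion could be selected and Part 2 would be read on it. The individual tests in Part 2 carry the same defect, with no majority rule to filter them.

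**Working it through.** **Inputs from the article.** One session per condition per subject; activity of up to 15 minutes; loosest level 0.05; 40 subjects (section 3.2) or 36 (section 4.1). The only computed design figure is the 36, and it reproduces: 1.96² × 0.25 / 0.15² = 42.68, and 42.68 / (1 + 41.68/200) = 35.3, rounded up to 36. It is a precision calculation for a proportion and does not bear on this test. For the permutation test the article gives no error rate beyond the nominal level.

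**Assumptions, because the article gives no figures.** Windows per session: 7, 15, 30 or 90 (about 2 min, 60 s, 30 s or 10 s each). Serial dependence: AR(1) with lag-1 correlation ρ from 0 to 0.9. Session offset: SD 0 to 1, in units of the within-session window SD. Two-sided tests. Majority: at least 21 of 40.

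**Step 1, limiting case.** With the session as the exchangeable unit there is one unit per condition, hence two arrangements with the same absolute difference. The smallest two-sided p-value per subject is 1.0. No window length changes this.

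**Step 2, per-subject rate f.** Two sessions with no true difference were simulated 2,000 times per setting, with 499 permutations each. Approximate analytic checks:

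- Serial correlation inflates the variance of the mean by V = (1+ρ)/(1−ρ). The rate is then 2 × [1 − Φ(1.96/√V)]. For ρ = 0.5, V = 3 and the rate is 26%. For ρ = 0.7, V = 5.67 and 41%. For ρ = 0.8, V = 9 and 51%.
- A session offset of SD s with m independent windows gives V = 1 + m·s². For m = 30 and s = 0.5, V = 8.5 and the rate is 50%. For m = 15, V = 4.75 and 37%.

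**Step 3, majority rule for one null variable.** Ignoring direction, as the rule is written: P(X ≥ 21) with X ~ Binomial(40, f). Requiring the same direction: 2 × P(X ≥ 21) with X ~ Binomial(40, f/2), since a null difference goes either way equally often.

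| Assumed dependence | f | Passes, either direction | Passes, same direction |
|---|---|---|---|
| None, 30 windows | 5.6% | negligible | negligible |
| ρ = 0.3, 30 windows | 15.5% | 6 × 10⁻⁸ | negligible |
| ρ = 0.5, 30 windows | 26.4% | 0.0004 | < 0.00001 |
| ρ = 0.7, 30 windows | 42.3% | 0.13 | 0.00003 |
| ρ = 0.8, 30 windows | 52.4% | 0.56 | 0.0007 |
| Offset 0.5 SD, 15 windows | 34.4% | 0.014 | < 0.00001 |
| Offset 0.5 SD, 30 windows | 50.6% | 0.47 | 0.0004 |
| Offset 1 SD, 30 windows | 70.2% | 0.99 | 0.04 |

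From 7 to 90 windows and without an offset, f stays at 14–16% (ρ = 0.3), 24–27% (0.5), 42–43% (0.7) and 52–55% (0.8). With an offset it rises with the number of windows. With 36 subjects and at least 19 significant, the results are similar.

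**The case against.** The strongest case on the other side has five parts.

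1. *The dependence is assumed.* Window length, autocorrelation and session offset are not in the article, and a condensed article may leave the window length and the permutation scheme to a fuller plan. A reader might infer that the error rate is known to be several times 5%. The documents do not support that as a fact; it follows only under assumed dependence. What remains is that no choice of window or block cures one session per condition.

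2. *The majority rule is a real screen.* A reader might infer that null variables would routinely be selected. At ρ of 0.5 or less without an offset, the chance is below 0.1%. If the same direction were required, it would be about 5% or less in every case tabulated. This stands, and it is why the selection figures must be shown as a range. But the rule as written does not mention direction.

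3. *The baselines may be used.* A reader might infer that the plan compares raw session values. The article does not say so; whether the tested quantity is baseline-referenced is left open. Using the baselines would not rescue the per-subject test, however. Subtracting one constant per session leaves the serial correlation in place and turns baseline noise into a shared offset.

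4. *Order is counterbalanced.* This works across subjects and cannot correct a test done within one subject.

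5. *Part 1 is descriptive, and Part 2 uses different sessions.* This stands in part. A poor selection does not inflate the error of the Part 2 group test. It damages the interpretation of the variables on which that test is read.

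**Conclusion.** The point holds in a conditional form. The individual p-values in both parts are not valid, because the shuffled windows are not exchangeable between two single sessions. This follows from the design and needs no assumed number.

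The size does rest on assumptions. At nominal 5%, the per-subject false-positive rate runs from about 14% at lag-1 correlation 0.3 to about 52% at 0.8. A session offset of 0.5 window SD gives about 35% with 15 windows and 50% with 30.

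The consequence for selection, ignoring direction, runs from below 0.1% (correlation 0.5 or less, no offset) through about 13% (0.7) and 55% (0.8) to over 99% (offset 1 SD, 30 windows). So the plan does not guarantee a false selection, but nothing in the stated test guards against one when correlation is high or sessions differ in level. The individual tests in Part 2 have no majority screen, so there the inflated rate applies directly.

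**What to change.** In section 4.2, replace the per-subject test as the basis for selection:

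- For each subject and variable, compute the activity value minus that session's own baseline, in sessions 1 and 2.
- Take one signed difference, session 1 minus session 2, per subject.
- Select variables by a group-level sign-flip permutation test, or a Wilcoxon signed-rank test, on these 36 to 40 differences. The subject is then the exchangeable unit.
- Report beside it the share of subjects who move in the same direction.
- In both parts, report individual-level comparisons as descriptive effect sizes without significance stars. Block permutation is not an adequate substitute: it handles serial correlation but not the session offset.

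The cost is analysis wording and code, since the baselines are already recorded. There are two drawbacks. No individual-level significance can be claimed. And the group test targets a common direction of change, so a variable that responds in opposite directions in different subjects may be missed.
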